### Trial management and governance

Clinical notes, measures, and therapy recordings are stored in a locked filing cabinet in a locked office at Philipps-University Marburg. Consent forms are stored separately from data. Data is entered into an SPSS spreadsheet maintained by the trial manager (ND), stored securely on Philipps University Marburg server. Only individuals authorized by the principal investigator have access to the database. We design this first pilot study for conciseness and minimizing risk. Therefore, no formal data monitoring committee has been organized. The completeness and correctness of the data storage will be checked and ensured every two weeks by the study coordinator (ND). The results will be reported to the leading investigators (HC and ELB).

Published material will not contain patient-identifiable information. The datasets generated and/or analyzed will be stored in a repository at Philipps-University Marburg. Anonymized data may be accessed and analyzed by members of the project with researchers collaborating with team members on the analysis of these data. Therefore, external researchers wishing to access the data for future projects or analyses must do so via request to the principal investigator (ND).

## Discussion

The first aim of this study is to apply CBASP, which is well-developed and already evaluated for adults, for the first time in a version modified specifically for children and adolescents with depressive disorders. We aim to focus on integrating caregivers and interpersonal relationships to treat depressive disorders in children and adolescents in an age-appropriate manner relying on the CBASP treatment approach. Attachment and the relationship between parents and children are areas of high relevance in the treatment of depressive disorders and should be considered especially in the context of dysfunctional interaction behaviors or even childhood maltreatment. For this reason, CBASP@YoungAge focuses on involving the actual caregivers as well as on the processing of earlier relationship experiences and their impact on the disorder (“significant others”). We expect that this treatment will result in a stronger alleviation of the young person’s depressive symptoms, and in improved interpersonal behavior of children and caregivers, thus leading to a long-term improvement in the patients’ symptomatology. Since there are so few therapeutic approaches that effectively treat depression in this age group [21], and the current treatment programs reveal such low effect sizes [20], we see an urgent need to investigate a therapy program that addresses both the present symptoms of young people and the interpersonal problems with their actual caregivers. CBASP@YoungAge offers this opportunity and is thus a promising approach to treat depression in children and adolescents.

In addition to the results in terms of clinical relevance, the practicality and feasibility of the trial are also important. Those results will allow us to evaluate the feasibility and effectiveness of this treatment program and will provide valuable information on whether this modular and interaction-focused treatment can actually be implemented in other outpatient treatment settings at different locations. In particular, its feasibility from the perspective of the patients and their relatives, as well as from the therapists will be examined. Any obstacles can be removed and necessary changes can be made according to the results. Furthermore, building on this non-randomized pilot study’s results, we will be able to plan a large controlled randomized trial. Whether this is applicable depends on various factors and aspects. Central is whether the CBASP@YoungAge treatment does not cause harm to patients or relatives. Furthermore, it is important to know whether recruitment is possible in order to implement a larger study and if the therapy can be carried out and terminated by therapists and patients with a reasonable amount of effort. Aspects that are also considered in the evaluation of feasibility are cost-effectiveness, duration of therapies and study as well as effectiveness and feasibility of data management.

However, the results we expect from this pilot study are also hampered by certain limitations. Firstly, it is based on a quasi-experimental design. Since all participants in the intervention group are treated in the Marburg outpatient clinic and all TAU participants are treated in either the outpatient clinic in Bochum or Landau, no randomization is possible, which also means that study-site effects cannot be excluded. Secondly, due to the Corona pandemic, we could not start collecting data at all three outpatient clinics at the same time. That makes seasonal side effects possible between the intervention and control groups (also due to the respective pandemic situation). Third, the design is focused on assessing the feasibility of the treatment program. However, this leads to the fact that not all relevant aspects, e.g., the therapeutic alliance, can be captured. Fourth, because of the ongoing pandemic situation, we were unable to define numeric progression criteria. Regarding the various safety regulations, the rules for outpatient psychotherapy were and are frequently changed. Thus, it was not possible to predict exactly how recruitment, duration of therapy, or even data management would proceed. However, we will carefully monitor the different progression criteria to determine whether progression is feasible and to learn how to adapt and improve progression in a large-scale RCT trial.

Finally, the study’s design means that patients and therapists cannot be blinded which could create some bias among therapists and patients. However, we are trying to mitigate possible biases resulting from the lack of blinding by ensuring that the clinical evaluations are not done by us study therapists but rather by independent blinded raters. Against the background of the first investigation of this intervention within the framework of a phase 1/phase 2 clinical trial, these limitations appear in general justifiable.

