### Participants and sample size

Eligible participants are aged between 10 and 21 years and meet the criteria for depressive disorders, based on DSM-5 [51]. Inclusion is based on a structural clinical interview (Kinder-DIPS, parent or child version [52]). A participating caregiver is mandatory in the CBASP@YoungAge group, whereas caregiver participation in the TAU groups is not requested beyond the legal requirements. As psychotherapy is conducted in German, children and participating parents need to be sufficiently fluent in German. Further, sufficient cognitive level of participating children/adolescents is required for the patients to be able to follow the cognitive interventions. Since intelligence tests are part of the standard diagnostics in the participating outpatient clinics, this criterion is operationalized by an IQ of ≥ 80.

We exclude children or adolescents in case of ongoing psychotherapy, acute suicidality, or a disorder expression requiring a different and non-depression focused treatment (e.g., traumatic disorder, schizophrenia, or bipolar disorders) or an inpatient stay. We do not exclude comorbid disorders or ongoing psychopharmacotherapy to enhance the external validity and generalizability of our findings. In case of outpatient housing, youth in the CBASP@YoungAge treatment group can nominate a different adult to participate in the sessions, as long as there is at least one significant person able and willing to join treatment sessions. If more than one person wants to participate, that is also possible.

Sample size calculations are guided by the considerations of Hertzog [53]. Thus, the planning of a larger study by this investigation was important, as well as the capacities of the centers involved and the sample size and drop out rate of other comparable studies [54, 55]. We aim to recruit 44 participants (22 per treatment arm). Assuming a 60% retention rate during the trial [56], this will lead 38 treatment completers with complete data.

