### Outcomes

Assessments are at pre-treatment (T1), post-treatment (T2) and follow-up at 6 months (T3) (see Fig. 1 for overview). Assessments are face-to-face (clinical interview) or paper-pencil questionnaires and filled out by index patients and/or their caregivers/significant others.

Primary outcomes are, first, the feasibility of the CBASP@YoungAge treatment program. This includes both practicability in the outpatient setting for therapists and suitability for patients and family members, primarily measured by continuous process evaluation (therapists, patients, parents), therapist adherence, patient dropout rate, and recruitment rate during the study and treatment. Second, change in depressive symptomatology between pre- and post-assessment is a primary endpoint, with change measured by the clinical interview (child DIPS, parent or child version) and the Mood and Feelings Questionnaire (MFQ).

Secondary outcomes are the interpersonal behavior between caregiver and children (Impact-Message-Inventory for children and adolescents, IMI@YA), the global health of both caregivers and participating children (KIDSCREEN; Positive mental health questionnaire, PMH), parents' mental health (Brief-Symptom-Inventory, BSI), and parenting quality (Parenting Questionnaire, EFB).

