## Conclusion

This pilot study is the first to explore the feasibility and effectiveness of CBASP adapted for children and adolescents suffering from depression. Considering the current low treatment outcomes [15] as well as the high proportion of interactional problems in the context of depressive disorders [77, 78], this treatment program is highly relevant. It will provide important knowledge on the feasibility and effectiveness of this program, and reveal the potential of including caregivers in psychotherapy. A multi-center randomized controlled study is being planned based on this study’s results, with the long-term aim of improving psychotherapeutic care for young patients with depression while preventing persistent courses of depressive disorders.

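### Feasibility is the first primary outcome and the planned RCT depends on it, but no result on its metrics is pre-specified as stop, amend or go

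*Protocol article*

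**What the plan says.** The Outcomes section states: "Primary outcomes are, first, the feasibility of the CBASP@YoungAge treatment program". The measures it names are the continuous process evaluation and "therapist adherence, patient dropout rate, and recruitment rate during the study and treatment". No target is attached to any of them.

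The Statistical analysis section lists the descriptive quantities: attrition and its reasons, refusals, completed adherence checks, missing data, and the share of patients reaching eight or more sessions in each arm. None carries a required value. The eight-session figure defines an adequate dose for one patient; the proportion of patients who must reach it is not given.

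On moving to a large RCT, the Discussion says "Whether this is applicable depends on various factors and aspects". It then names absence of harm as central, asks whether recruitment is possible, and asks "if the therapy can be carried out and terminated by therapists and patients with a reasonable amount of effort". The Conclusion says: "A multi-center randomized controlled study is being planned based on this study’s results".

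The limitations paragraph of the Discussion says that "because of the ongoing pandemic situation, we were unable to define numeric progression criteria". It explains that frequently changing rules for outpatient psychotherapy made recruitment, therapy duration and data management hard to predict. It goes on: "we will carefully monitor the different progression criteria to determine whether progression is feasible".

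**The concern.** A primary outcome that feeds a decision needs a rule linking the observed result to that decision. Here the measures are fixed in advance but the rule is not. The limitations paragraph says both that numeric criteria were not defined and that progression criteria will determine whether to proceed. Measures without values can inform such a judgement; they cannot determine it.

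What is at stake is how the pilot's main conclusion can be read. If 15 of 22 patients stay to the post-treatment assessment (T2), the plan does not say whether that supports the RCT, calls for changes or argues against it. Whoever decides will do so knowing the result, and readers cannot tell a standard that was met from one chosen to fit.

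This is not a matter of detail left to an analysis plan that is not shown. The article states outright that the criteria were not defined.

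**Working it through.** **Inputs.** From Participants and sample size: 44 recruits, 22 per arm, 60% retention, 38 completers. From Trial status: first inclusion 9 November 2020, preliminary analysis December 2022. The cut-offs and the true retention rates used in step 3 are illustrative assumptions.

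**1. Does the plan hold an implicit benchmark?** The only numeric expectation for a feasibility measure is the sample-size sentence: "Assuming a 60% retention rate during the trial", 38 completers are expected from 44 recruits.

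- 44 × 0.60 = 26.4, about 26 completers, not 38.
- 38 / 44 = 0.864, so 38 completers means 86% retention.
- 38 / 0.60 = 63.3, so 38 completers at 60% retention needs 64 recruits.

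The figure does not reproduce. It is also a sample-size assumption pooled over both arms, so it cannot stand in for a pass mark in the intervention arm.

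**2. Will the data settle the matter without a rule?** The exact (Clopper-Pearson) 95% interval for x of n runs from the 0.025 quantile of Beta(x, n − x + 1) to the 0.975 quantile of Beta(x + 1, n − x). With n = 22:

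- 13/22 = 59.1%: 36.4% to 79.3%
- 15/22 = 68.2%: 45.1% to 86.1%
- 19/22 = 86.4%: 65.1% to 97.1%

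The first and last intervals overlap from 65.1% to 79.3%. At this size, no plausible mid-range result points one way by itself.

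**3. What could a rule do at n = 22?** With X ~ Binomial(22, p), take go as X ≥ 18, stop as X ≤ 13 and amend as 14 to 17. P(stop) = 1 − P(X ≥ 14).

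| True retention p | Go: P(X ≥ 18) | Stop: P(X ≤ 13) | Amend (remainder) |
|---|---|---|---|
| 60% | 0.027 | 1 − 0.454 = 0.546 | 0.427 |
| 80% | 0.543 | 1 − 0.980 = 0.020 | 0.437 |
| 86% | 0.814 | 1 − 0.998 = 0.002 | 0.184 |

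The go cut rarely passes a programme with 60% retention. The stop cut, however, fires more often than not at 60%, the plan's own stated assumption. If 60% is meant to be acceptable, that cut is too high.

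A stop cut at 10 or fewer gives 1 − 0.879 = 0.121 at 60%. The price is a weaker stop at a true 50%: 1 − 0.584 = 0.416, against 1 − 0.143 = 0.857 for the cut at 13. The choice turns on what retention the team regards as acceptable, which is why step 1 must be resolved first.

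**4. How blind would cut-offs set now be?** The preliminary analysis falls about 25 months after first inclusion. Under the adherence and trial management sections, the study team reviews session forms monthly and the coordinator checks the data every two weeks. The team will therefore have seen much of the accruing recruitment, dropout and adherence.

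**The case against.** The gap is disclosed, a reason is given, and the authors call their limitations justifiable overall. That stands: this is an admitted design weakness, not a hidden error. Disclosure does not remove the inconsistency, since the same paragraph still assigns the criteria a deciding role.

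A reader might infer that any result could be called feasible, or that the trial cannot return a negative answer. The documents do not support that. The Discussion names conditions that can fail, with harm called central, and the Statistical analysis section fixes in advance what will be reported. The decision is discretionary, but it is not bound to be positive.

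A reader might also take 60% and 86% as rival pass marks and measure the harm by the gap between them. At a true retention of 70%, P(X ≥ 14) = 0.81 and P(X ≥ 19) = 0.07. That contrast reflects the separate error in the sample-size sentence, which sets no pass mark and pools both arms. It does not measure the effect of lacking criteria.

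The pandemic explanation names recruitment, therapy duration and data management. Changing rules could plausibly affect dropout and adherence too, so it should not be dismissed as irrelevant to them. Even so, uncertainty about what will happen does not prevent a team from stating what it would accept, and an amend band leaves room for disruption.

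The strongest objection is to the remedy: cut-offs written in late 2022 would not be blind to accruing data. That is correct. It limits what the fix achieves and has to be stated alongside it.

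**Conclusion.** The point holds. Feasibility is primary and the RCT is conditional on it, yet no result on dropout, recruitment, therapist adherence or process evaluation is pre-specified as stop, amend or go. On those measures the progression decision is left to judgement after the data are seen.

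Its size cannot be put as a single error rate, because without a rule there is none to compute. What can be said is that 22 patients give intervals about 32 to 43 percentage points wide (97.1 − 65.1 and 79.3 − 36.4), and that the plan's only retention expectation contradicts itself. Neither the data nor the plan supplies the missing standard.

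The precision figures assume that all 22 intervention patients are enrolled and that their retention outcomes are independent. The go and stop figures also depend on the illustrative cuts. The weakness should be corrected, but it does not affect data collection or patient safety.

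**What to change.** 1. Reconcile the retention figures in Participants and sample size (60% of 44 is about 26, not 38), and state which retention is expected and which is acceptable.
2. Before the December 2022 preliminary analysis, replace the limitations statement with a dated stop/amend/go table. Give one pair of cut-offs for each of intervention-arm retention to T2, recruitment, therapist adherence and T2 data completeness.
3. Report the operating characteristics of each pair. For retention, go at 18/22 or more and stop at 13/22 or fewer is a worked example only; lower the stop cut if 60% is meant to be acceptable.
4. State beside the table that the cut-offs were set after recruitment began and with open monitoring of accruing data.
5. If the team declines to set numbers, reword the Discussion, including its limitations paragraph, to say that the pilot describes feasibility and does not by itself determine whether the RCT goes ahead.

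The cost is one short table and a corrected sentence, with no new data, staff or patients. There are two downsides: the cut-offs are not fully blind, and the trial can then miss its own mark. The fallback in item 5 costs only wording, but gives up the claim that the pilot decides progression.

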### Study setting

As CBASP@YoungAge is an outpatient treatment program, the intervention group is implemented at the Child and Adolescents Psychotherapy Outpatient Clinic Marburg (KJ-PAM, Philipps-University Marburg) while the TAU control groups are implemented at the Center for Child and Adolescent Psychotherapy (Outpatient Clinic, Ruhr-University Bochum) and the Landau Psychotherapy Outpatient Clinic for Children and Adolescents. All outpatient clinics are based in Germany and leading psychotherapy institutions invoice the German health insurance companies. The therapists are psychotherapy trainees.

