**Fig. 2 Fig2:**

Timeline of the study

The psychotherapeutic process is evaluated during treatment by the study therapists. If difficulties arise during treatment, the study therapists contact the study team in the appropriate outpatient clinic. The intervention or follow-up is discontinued if the caregivers or patients withdraw consent or a different treatment becomes necessary. The therapy process is also discontinued if the trial has to be unexpectedly canceled, or if the study coordinator decides it is necessary to discontinue, for example in case of adverse events. The risk management information below provides further information. The date and reason for discontinuation or drop-outs after screening will be documented.

After treatment completion, trained therapists will carry out regular post-assessments who were not involved in the treatment. Participants have to wait for at least 6 weeks before booster sessions are allowed when needed. If follow-up treatment (e.g., for comorbidities) appears to be necessary during booster sessions, that can be implemented as part of regular outpatient treatment, and will be documented (see Fig. 3 for the study flow).

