### Randomization, allocation concealment, and blinding

Assignment to the two study arms is non-randomized and the allocation is not blinded. The pre- and post-assessments will not be blinded, but rather done by trained psychotherapists who are independent and did not provide treatment in either of the study arms to the respective families.

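### The Methods say the pre- and post-treatment assessments are unblinded, while the Discussion relies on blinded raters to limit bias; the two statements must be reconciled

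*Protocol article*

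**What the plan says.** Three places in the protocol article describe who assesses outcomes.

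- **Methods, Randomization, allocation concealment, and blinding.** "Assignment to the two study arms is non-randomized and the allocation is not blinded". On outcome assessment it continues: "The pre- and post-assessments will not be blinded, but rather done by trained psychotherapists who are independent". The independence is then defined: the assessors "did not provide treatment in either of the study arms to the respective families".
- **Methods, Recruitment and procedure (text following Fig. 2).** "trained therapists will carry out regular post-assessments who were not involved in the treatment". Blinding is not mentioned.
- **Discussion, limitations.** After conceding that patients and therapists cannot be blinded, the article says "we are trying to mitigate possible biases resulting from the lack of blinding" and gives the means: "the clinical evaluations are not done by us study therapists but rather by independent blinded raters".

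On sites, the Study setting section says that "the intervention group is implemented at the Child and Adolescents Psychotherapy Outpatient Clinic Marburg" and places the treatment-as-usual (TAU) arm in Bochum and Landau. The Discussion confirms that "all participants in the intervention group are treated in the Marburg outpatient clinic".

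The Outcomes section makes pre-to-post change in depressive symptoms a primary endpoint, measured by the Kinder-DIPS interview and the Mood and Feelings Questionnaire (MFQ). The Statistical analysis section bases response and remission on the Kinder-DIPS.

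**The concern.** The Methods and the Discussion make incompatible statements about the same interviews, and the one in the Discussion is the more favourable. It is also the only measure that the article offers against bias from lack of blinding. The article then judges its limitations to be acceptable overall, so that judgement leans in part on a protection that the Methods deny.

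The Kinder-DIPS leaves room for judgement. According to its description, the interviewer may add clarifying questions, and the diagnostician chooses whether to interview the child, the caregiver or both. An interviewer who knows the arm can affect the result by either route, without intending to.

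The other symptom measure offers no blinded backup. The MFQ is a questionnaire with self-report and caregiver versions, and the Discussion accepts that patients are not blinded. If the interviewers are not blinded either, neither instrument for the primary symptom endpoint is shielded from knowledge of treatment.

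This matters beyond the pilot. The Objective section expects greater symptom relief than under TAU, the arms are to be compared by ANCOVA, and the data are to inform power calculations for a randomized trial. A reader who believes that the interviews were blinded would put too much trust in a between-arm difference on the Kinder-DIPS.

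**Working it through.** No formula applies and the plan gives no figure to reproduce. The check sets the statements side by side and asks whether any reading lets them all stand.

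| Question | Methods: blinding section | Methods: procedure | Discussion: limitations |
|---|---|---|---|
| Did the assessor treat the family? | No | No | No |
| Is the assessor blinded? | No, stated outright | Not addressed | Yes, stated outright |
| Time points covered | Pre and post | Post | Not restricted |

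**Step 1: do the statements concern the same assessments?** The Outcomes section lists two modes: the face-to-face clinical interview and paper questionnaires completed by patients or caregivers. The Methods sentence concerns assessments carried out by psychotherapists, and the Discussion sentence concerns clinical evaluations by raters. Both descriptions fit the interview and not the questionnaires, so the subject is the same.

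**Step 2: can the time points separate them?** The Methods sentence does not name the 6-month follow-up, so raters could in principle be blinded at that visit only. The Discussion sentence has no such restriction, and the primary symptom endpoint runs from pre to post. This reading does not resolve the conflict where it matters most.

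**Step 3: is a masking procedure described elsewhere?** None is. The procedure section promises only that assessors took no part in treatment. Independence from treatment and ignorance of the arm are different properties: a colleague who never met the family can still know which programme the clinic delivers.

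**Step 4: what does the site structure add?** All intervention patients are in Marburg and all TAU patients are in Bochum or Landau, so clinic determines arm. Anyone who knows the patient's clinic knows the arm. Masking would therefore require raters to be unaware of the clinic, and no arrangement of that kind is mentioned.

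**Step 5: result.** The sections agree on independence and conflict on blinding. The conflict falls on pre-to-post Kinder-DIPS change and, at post-treatment, on response and remission.

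**The case against.** The strongest reply is that the Methods section, where blinding is specified, openly says that assessment is unblinded. The fault would then be one misplaced word in a limitations paragraph, perhaps used loosely for raters who were not involved in treatment. The trial is a non-randomized pilot, its feasibility analysis rests mainly on process evaluation in the intervention arm, and the article already admits that site effects cannot be excluded. This has force: unblinded assessment is a disclosed choice, and the fault is an inconsistency in the text. It does not make the correction unnecessary, because the misplaced word carries the article's only stated safeguard and touches a primary measure.

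Three stronger readings are tempting, and the document does not support them.

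- **That the raters certainly know the arm because clinic equals arm.** The article gives the treatment sites but does not say where raters are based. Raters kept unaware of the clinic are conceivable. The site structure makes unblinding likely without proving it; the case rests on the explicit Methods statement.
- **That there is no mitigation at all.** All three places agree that assessors did not treat the families they assess. That separation has value and survives.
- **That the bias can be given a size.** One could suppose lenient rating of 2 of the 22 planned intervention patients and obtain 2/22 = 9.1 percentage points on remission. The 2 is arbitrary, so the result says nothing about this trial.

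Nor does the document prove which statement is true. The Methods text is the operative one and the procedure section is compatible with it, so it is the more plausible, but the SPIRIT checklist in Additional file 1 is not available here to settle the matter.

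**Conclusion.** The point holds as an internal contradiction on a stated design property. The pre- and post-treatment Kinder-DIPS interviews cannot be both unblinded and done by blinded raters. On the document's own evidence, the unblinded description is the better supported: it is explicit, it stands in the section that governs blinding, and no masking procedure appears anywhere.

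What fails is the blinding part of the mitigation, so the protection against detection bias is weaker than the Discussion describes. The size of any bias cannot be estimated from the document. The conclusion assumes that the Discussion's clinical evaluations are the Kinder-DIPS interviews named under Outcomes; it needs no assumption about where raters work.

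**What to change.** Reconcile the two sections, in one of two ways.

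1. **If no masking procedure exists:** delete the word for blinding from the Discussion sentence. State that raters are independent of treatment but not blinded to arm, and list unblinded Kinder-DIPS assessment as a limitation. Report and interpret Kinder-DIPS change, response and remission as unblinded outcomes, including when they inform the randomized trial.
2. **If a masking procedure does exist:** correct the Methods statement and describe how raters are kept unaware of both clinic and arm, and at which time points.

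The cost is a wording correction and a weaker stated protection against detection bias. Under Trial status, the preliminary analysis was foreseen for December 2022 and the end of follow-up for July 2023, after the article appeared in July 2022, so the correction could be made before results were reported.

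Exchanging raters between clinics by telephone or video is not a good substitute. A Marburg rater assessing another clinic's patients would see only TAU patients and so would know the arm. It would also move later interviews away from the face-to-face mode given under Outcomes while the trial is running.
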